# Assessing and reporting adverse events and reactions

Serious adverse events (SAEs) and adverse events (AEs) are collected in accordance with what is outlined below, as per the guidelines from SOMREC and in accordance with the SOP.

## Adverse events

In this trial, an adverse event constitutes any untoward medical occurrence in the clinical trial subject at any dose of the LNS nutritional intervention product and which does not necessarily have a causal relationship with this treatment. The AEs will be recorded in the CRF.

- All reported or observed adverse events (AEs) taking place during the intervention period of the trial will be recorded; this is from the time informed consent is given, until the time when the participant is discharged from the study.
- The PI will report all AE records to the sponsor biannually. The sponsor will keep detailed records of adverse events.
- AEs will be reported to SOMREC in the annual progress reports.

## Serious adverse events:

A serious adverse event (SAE) in this study is any untoward medical occurrence that at any dose of the LNS nutritional intervention: results in death, is life-threatening (immediate risk of death), results in persistent or significant disability or requires inpatient hospitalisation or prolonged hospitalisation.

- SAEs occurring to a study participant during the trial period will be reported to the sponsor within two working days of becoming aware.
- SAEs will be reported to SOMREC within 7 calendar days of becoming aware of the event. If more information concerning the event becomes available, a follow-up report will be submitted to SOMREC within 14 calendar days of becoming aware of the event.
- Serious adverse events occurring after a subject is discontinued from the study will NOT be reported unless the investigator suspects that the event is related to the study investigational products.

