# Reference group

This study includes a group of 150 un-supplemented stunted children as a reference group. These children will not receive an intervention product, but instead will continue with the family diet and will receive locally adapted nutrition counselling as well as monitoring and regular follow-up over the intervention period.

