## Tertiary outcomes

Blood hormone markers

- Insulin-like Growth Factor-1 (IGF-1)
- Insulin

Blood markers of systemic inflammation

- C-reactive protein (CRP)
- Alpha-1-acid glycoprotein (AGP)

Blood markers of enteric function

- Citrulline.
- Blood markers of micronutrients status Iron (ferritin and soluble transferrin receptor)
- Vitamin B12
- Folate
- Vitamin A (retinol binding protein)
- Stool markers of intestinal inflammation Myeloperoxidase (MPO)
- Neopterin (NEO)
- Alpha-1-antitrypsin (AAT)

Gut microbiota

Safety, morbidity and loss to follow-up

- Proportion deteriorated to MAM, measured as WHZ ≤ -2 and >-3 or MUAC ≤ 125 and >115mm) and proportion deteriorated to SAM, measured as WHZ <-3, MUAC <115mm or presence of nutritional oedema.
- Proportion of participants who die during the study period (mortality)
- Number of morbidity episodes, duration and severity (diarrhea, pneumonia, fever, malaria, other) during the intervention period
- Proportion lost to follow-up during the study period

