## Data safety monitoring board

An independent data safety monitoring board (DSMB) has been established and all members have consented to participation on the board. The DSMB consists of four members:

- Chairman: [name], Paediatrician, World Health Organisation, Sierra Leone.
- Board Member: [name], PhD, Assistant Professor and MSc Nutrition for Global Health Programme Director, London School of Hygiene & Tropical Medicine, London, UK.
- Board Member: [name], PhD, bioethicist, senior lecturer at the College of Health Sciences and Chair of Biomedical Sciences Higher Degrees and Research Ethics Committee, Makerere University.
- Board Member: [name], BPharm, MSc and PhD in Medical Statistics. Honorary Assistant Professor at the Department of Medical Statistics, London School of Hygiene & Tropical Medicine, London, UK

The DSMB is a group independent of the study organisers who will monitor safety parameters. They will receive unblinded data including individual case fatality reports, SAEs and reasons for termination of participants. Based on this information, the DSMB will decide if the study can continue or if any actions are needed. There is one pre-defined stopping rule for the unlikely risk of high mortality: p< 0.01 after inclusion of 300 children. The safety monitoring board will have access to the randomization code and will not be blinded to the treatment of the children.

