## Discontinuation of participation in the study

Parents or caregivers are allowed to withdraw their child from the investigation at any time for whatever reason. The Investigator also has the right to discontinue participant investigations at any time if they deem that it is in the best interest of the participant or if non-compliance with the clinical protocol impacts on the scientific integrity of the clinical study. Possible reasons for premature withdrawal of a study participant include:

- Non-compliance with the clinical protocol impacting on the scientific integrity of the clinical study.
- If a child’s safety and well-being is compromised by further participation

In case of patient withdrawal, the CRF will be completed up to the point of patient withdrawal and all available data will be used in data evaluation/statistics. Withdrawn patients will not be replaced.

All participants requiring hospital attention will be referred for treatment. If a child is referred for hospital treatment, attempts will still be made to follow-up on the child wherever possible.

Early termination of a child from the study occurs due to the following reasons: the investigator sees fit to discontinue participation, the caregiver wishes to discharge, death and loss to follow-up.

If a child dies while enrolled in the study, the medical cause will be identified (if possible) by verbal autopsy, noted in the CRF and reported to the sponsor (as per the SAE reporting SOP).

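### SAE and death reporting ends at discontinuation, although 12-week mortality is an outcome and the basis of the only stopping rule; the AE and SAE definitions also leave out the reference group if read literally

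*Protocol*

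**What the plan says.** Five places in the protocol bear on this.

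- **Section 26, Serious adverse events.** An SAE is defined as "any untoward medical occurrence that at any dose of the LNS nutritional intervention: results in death", or one of the other listed serious consequences. One bullet requires SAEs in study participants to be reported to the sponsor. The last bullet sets a cut-off: "Serious adverse events occurring after a subject is discontinued from the study will NOT be reported". The only exception is for events in which a link to the products is suspected. The AE definition in the same section is also tied to a dose of LNS, but its first bullet records every reported or observed AE from informed consent to discharge.
- **Section 28, Discontinuation of participation in the study.** One listed reason for premature withdrawal is "If a child’s safety and well-being is compromised by further participation". After withdrawal the CRF is not continued. Verbal autopsy and reporting of a death to the sponsor are described for a child who dies while enrolled, and they follow the SAE reporting SOP. Children referred to hospital are still to be followed where possible.
- **Section 17, Tertiary outcomes, and Section 22, Deterioration and loss to follow-up.** The proportion of participants who die is an outcome. It is defined over the 12-week intervention period and is not restricted to children still enrolled.
- **Section 24, Data safety monitoring board.** The DSMB receives case fatality reports, SAEs and reasons for termination. "There is one pre-defined stopping rule for the unlikely risk of high mortality", set at p < 0.01 after 300 inclusions. The test and the groups compared are not stated.
- **Section 13, Reference group.** "These children will not receive an intervention product, but instead will continue with the family diet".

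**The concern.** The mortality outcome and the stopping rule are both framed over randomised participants for 12 weeks. The reporting rules follow a child only while it is enrolled. A child discontinued at week 4 who dies at week 9 belongs in the mortality proportion, but no section requires that death to be sought, recorded or passed to the DSMB. The exception to the cut-off presupposes that the investigator knows of the event and judges its cause, so the bullet also excludes events that are known.

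The loss need not be random. Compromised safety is a stated reason for withdrawal, and such children are plausibly at higher risk afterwards. A statistical analysis plan cannot repair this, because the data would never have been collected.

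The definitions raise a separate matter. If an SAE requires a dose of LNS, an event in an unsupplemented child is not an SAE on a literal reading. That conflicts with the bullets that cover every study participant.

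**Working it through.** **1. Is there another route by which a death after discontinuation would be captured?**

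| Possible route | What the protocol provides | Covers a discontinued child? |
| --- | --- | --- |
| SAE report | Stops at discontinuation unless relatedness is suspected | Only through the exception |
| CRF | Closed at withdrawal | No |
| Verbal autopsy and death report | Children who die while enrolled | No |
| Case fatality reports to the DSMB | Listed, but no separate collection procedure described | Not shown |
| Follow-up after hospital referral | Continues where possible | Only for referred children |
| Phone calls and home visits | Exist for appointments, health and missed visits | Not stated |

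No section provides for vital status to week 12 after discontinuation.

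**2. How many deaths would be missed at the 300-child look?** The protocol gives no mortality rate and no operating figures for the stopping rule, so there is no figure of its own to reproduce. Inputs:

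- Group sizes: 300/5 = 60 per group if allocation is equal, so 60 reference and 240 LNS.
- Discontinued share d: 10% (borrowed from the loss to follow-up allowed in Section 18) and 20% (assumed).
- Mortality m over 12 weeks: assumed, 0.2% to 5%.
- Share h of risk time falling after discontinuation: 0.5 (assumed).
- Discontinued children are assumed to have the same mortality as the others.

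Expected deaths missed = n × d × m × h.

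- m = 1%, d = 10%: reference 60 × 0.10 × 0.01 × 0.5 = 0.03; LNS at most 240 × 0.10 × 0.01 × 0.5 = 0.12.
- m = 5%, d = 20%: reference 60 × 0.20 × 0.05 × 0.5 = 0.30; LNS at most 240 × 0.20 × 0.05 × 0.5 = 1.20.

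The LNS figures are upper limits because some of those deaths might be reported under the exception. If discontinued children have higher mortality than the rest, all these counts rise in proportion.

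**3. How far could the exception alone separate LNS from reference?** If a share q of LNS deaths after discontinuation is reported as suspected related and no reference death is, the artificial difference in observed mortality is m × d × h × q. The largest value is at q = 1.

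- m = 1%, d = 10%: 0.01 × 0.10 × 0.5 = 0.05 percentage points.
- m = 5%, d = 20%: 0.05 × 0.20 × 0.5 = 0.5 percentage points.

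At q = 0 the difference is nil.

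**4. Could one missed death change the stopping decision?** Assume a two-sided Fisher exact test of reference (60) against pooled LNS (240).

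- 3 v 0 deaths: (60 × 59 × 58)/(300 × 299 × 298) = 0.0077, below 0.01.
- 2 v 0 deaths: (60 × 59)/(300 × 299) = 0.039, above 0.01.

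So one unreported reference death could reverse the result. The example is sensitive to the comparison chosen. An excess confined to LNS needs 23 v 0 (p = 0.0063) to cross, and one group of 60 against another needs 8 v 0 (p = 0.0061).

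**The case against.** A reader might infer something stronger: that the exception can never apply to a reference child, so deaths are undercounted unequally and the LNS v reference comparison is biased. The documents do not support this.

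- The cut-off applies to all five groups.
- The exception turns on what the investigator suspects, and the Blinding section says clinical staff are not told the allocation, reference status included. A relation could be suspected in a reference child.
- The risk assessment in Section 28 expects no product risk, so the share of LNS deaths reported through the exception should be near zero.
- Any residual difference would hide reference deaths and make LNS look worse. It would not conceal harm from the product.

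It would also be too strong to say that the sickest children disappear. Illness leads to referral with continued follow-up, and an SAE that prompts discontinuation precedes it and is reportable. The DSMB sees reasons for termination. Vital status in children who are truly lost is unknown under any reporting rule.

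On the definitions, the recording period starts at consent, before allocation, and the reporting bullet speaks of study participants. Both suggest that all children were meant. Section 26 also defers detail to an SOP that is not shown.

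These points dispose of the unequal-undercounting reading. They do not remove the mismatch. Children discontinued by the investigator, or withdrawn by caregivers who would still accept a phone call, can be reached, and the protocol does not ask for it. The only death-reporting procedure described is confined to enrolled children and runs through the SAE process.

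**Conclusion.** The concern holds as an internal inconsistency. Reporting ends at discontinuation or withdrawal, while mortality over 12 weeks is an outcome and the basis of the only stopping rule. Deaths may be missed in all five groups, possibly informatively. A material difference between LNS and reference arising from the relatedness exception is not shown.

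The expected loss is a fraction of a death in most of the scenarios examined, and about 1.5 deaths in total (0.30 + 1.20) in the most extreme. Because the rule may turn on very few deaths, one missing death could change the decision, but that is a possibility and not a likely event. These figures rest on assumed mortality, assumed discontinuation and its timing, and an assumed test and comparison.

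The LNS-dose wording of the AE and SAE definitions is a separate drafting fault. It is the more direct asymmetry for the reference group, but the surrounding bullets indicate that exclusion was not intended.

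**What to change.** Reconcile Sections 26 and 28 with Sections 17, 22 and 24:

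- Replace the last SAE bullet with a statement that deaths and SAEs are sought, and reported to the sponsor and the DSMB, for every randomised child to 12 weeks after inclusion, whether or not participation was discontinued, unless the caregiver refuses further contact.
- Align the discontinuation section, so that vital status and SAE data continue to be recorded after the rest of the CRF is closed, and death reporting is not confined to enrolled children.
- Define AE and SAE as an untoward occurrence in any enrolled child, irrespective of group.

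The cost is a change of wording in the protocol and SOP, plus a few extra contacts through the phone and home-visit follow-up already in place. Deaths in children who are truly lost, or whose caregivers refuse contact, will still be unknown.

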## Deterioration and loss to follow-up

*Proportion deteriorated to MAM or SAM* is the proportion of children who have deteriorated according to their status at inclusion. Either to MAM, measured as MUAC < 125 mm and ≥115mm or WHZ between -3 and -2, OR the proportion of children who have deteriorated to SAM, measured as WHZ <-3, MUAC <115mm or the presence of nutritional oedema.

*Proportion and qualification of morbidity* is the number of episodes, number of days with and the qualification of morbidity, during the 12 week intervention period. During the baseline clinical examination, signs and symptoms of the following are assessed: pneumonia (moderate or severe), diarrhea [acute watery (<14 days), acute bloody (<14 days), persistent (≥14 days)], fever (>38⁰C), common cold and other. The caregiver is given an exercise book at inclusion to be used to record morbidity information if the child visits another clinic or is admitted. If the caregiver brings this book to the clinic visit, it can be used to inform the clinician. In addition, caregiver perceived morbidity is assessed (when possible) with phone call follow-up over the 12 week intervention period.

*Mortality* is the proportion of participant deaths recorded during the 12 week intervention period.

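### The rule ending SAE reporting at discontinuation applies inside a child's own 12 weeks, so deaths that the mortality outcome and the DSMB need can go uncaptured

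*Protocol*

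**What the plan says.** Five parts of the protocol bear on this point.

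- **Section 26, Serious adverse events.** The definition covers an event that "results in death, is life-threatening (immediate risk of death"), among other criteria, so every death is an SAE. The last bullet then states: "Serious adverse events occurring after a subject is discontinued from the study will NOT be reported unless the investigator suspects that the event is related" (meaning product-related). It gives no time limit and does not separate a child who stops early from one who has finished the 12 weeks.
- **Section 28, Discontinuation of participation in the study.** One listed reason for withdrawal is that the child's "safety and well-being is compromised by further participation". After withdrawal, "the CRF will be completed up to the point of patient withdrawal". Verbal autopsy and notification of the sponsor are described for a child who dies during enrolment. The section also says that follow-up will still be attempted for a child referred to hospital.
- **Section 17, Tertiary outcomes.** Mortality is the "Proportion of participants who die during the study period (mortality"). It is not restricted to children still enrolled at death.
- **Section 22, Deterioration and loss to follow-up.** Mortality "is the proportion of participant deaths recorded during the 12 week intervention period".
- **Section 24, Data safety monitoring board.** On the DSMB members: "They will receive unblinded data including individual case fatality reports, SAEs and reasons for termination of participants". The section sets one stopping rule, for high mortality, at p<0.01 after 300 children have been included.

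**The concern.** A mortality outcome in a randomised trial should count deaths among all children randomised, over the same period in each arm. Section 17 sets it out that way. The reporting rule in section 26 works on a different basis: once a child is discontinued, a later death is passed on only if someone suspects the product. If that happens before the child's week-12 date, the outcome definition includes the death and the safety rules leave it out.

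Two features make this more than a matter of wording. First, one permitted reason for discontinuation is concern for the child's safety, so the children affected need not be a random subset. Second, the only exception to the rule depends on a suspected link to a product that one of the five groups never receives. Incomplete capture could therefore be uneven between supplemented and reference children. A statistical analysis plan cannot repair this later, because it cannot recover deaths that were never collected.

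**Working it through.** The protocol gives no figure for discontinuations or for deaths after them, so the check is to follow one child through the text.

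**Test case.** A child is randomised, the investigator discontinues participation between the week 4 and week 8 visits because safety is compromised, and the child dies before week 12. The investigator does not suspect the product.

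1. *Does the death belong in the outcome?* By section 17, yes: the child is a participant who died during the study period. By section 22, it counts only if it was recorded.
2. *Does the SAE route record it?* No. Section 26 excludes it, because the event follows discontinuation and is not suspected to be related. For adverse events in general, the same section ends recording when the child is discharged from the study.
3. *Does the CRF record it?* Section 28 requires no entry after withdrawal.
4. *Does the death procedure apply?* As described, it covers only a child still enrolled, so it does not reach this child.
5. *Does the hospital provision help?* Only if the child was referred for hospital care. Sections 14 and 28 then provide for attempted follow-up.
6. *Is there a vital-status check at week 12 for discontinued children?* None is stated. Section 10 provides home visits for participants who miss clinic visits, and sections 10 and 22 provide phone contact. Neither is said to continue after discontinuation.
7. *Does the DSMB learn of the death?* Section 24 gives it the reason for termination, so it sees the withdrawal. No stated route ensures that a report of the later death is generated.

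Steps 2 to 7 leave no assured route by which the death required at step 1 enters the data. This is an inference from several sections read together; no single sentence says that such deaths are dropped from the outcome.

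**The same child in the reference group.** Section 13 says reference children receive no product. Clinical staff are not to be told the group (section 20), so an investigator might in principle suspect a product the child never had, but that is not a dependable route. For a supplemented child the exception can operate as intended. The probability of capture after discontinuation may therefore differ between the groups even if their true death rates are equal.

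**After week 12.** For a child who completes the 12 weeks, a later unrelated event lies outside the section 22 mortality definition. The filter in section 26 causes no conflict there.

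**The case against.** The strongest reply has four parts.

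- **Reporting is not collection.** The bullets in section 26 say who is told and when; the outcome is defined in section 17 without a restriction. Section 26 also defers to a standard operating procedure and ethics-committee guidelines that are not shown. This is a fair point, and it is why the loss is described as possible. But section 28 separately stops the CRF at withdrawal, and section 22 counts only what was recorded, so the shown text offers no other assured source.
- **High-risk children are still followed.** A reader might infer that deterioration leads to discontinuation, so that the children most likely to die are systematically lost. The documents do not support that. Section 14 refers children who deteriorate to severe acute malnutrition for care, and sections 14 and 28 promise attempted follow-up of those needing hospital attention. This stands, and it confines the gap to children discontinued by the investigator or withdrawn by the caregiver.
- **The DSMB is not blind to the problem.** It receives reasons for termination and individual fatality reports, and it is unblinded. It can therefore ask about a child withdrawn for safety. That softens the consequence but does not supply the missing report.
- **The stakes are limited.** Mortality is one of many tertiary outcomes, and children with severe acute malnutrition or needing hospitalisation are excluded at entry, so deaths should be few. This bears on priority. It does not remove the contradiction.

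Nor is it a fault that causality is judged by blinded staff. That is an ordinary safeguard in a double-blind trial. The difficulty is that capture of a death within the 12 weeks depends on that judgement at all.

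**Conclusion.** The point holds as a conflict between sections 17, 22, 24, 26 and 28, confined to children who leave by investigator or caregiver decision before week 12. Read literally, the plan can omit deaths that its own mortality outcome includes and can withhold them from the body that applies the mortality rule. Capture may also differ between supplemented and reference children.

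The size is unknown. It is tempting to take the 10% loss to follow-up in section 18 as the number of children affected. That allowance is a sample-size margin and does not forecast discontinuations; a child who cannot be found has unknown status whatever the SAE rule says. A reader might also infer that one missed death would overturn the DSMB rule, or that the trial will report falsely reassuring mortality. Section 24 names neither a test nor a comparison, and the protocol gives no expected mortality, so neither claim can be shown.

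The conclusion rests on two assumptions: that the unseen operating procedures do not already require vital status for discontinued children, and that the section 26 rule is meant as written. If the procedures do require it, the protocol text still needs to be brought into line.

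**What to change.** Reconcile sections 17, 22, 24, 26 and 28 on one rule for data capture:

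- **Section 26:** deaths and SAEs in every randomised child are recorded and reported up to that child's scheduled week-12 date, regardless of discontinuation or suspected relatedness, unless the caregiver refuses further contact. The relatedness filter may stay for events after that date.
- **Sections 22 and 28:** vital status at week 12 is sought for every randomised child by the phone and home-visit routes already in place, within the same limit on consent. The CRF keeps a place for this after withdrawal.
- **Sections 17 and 22:** mortality is defined the same way in both places, over all randomised children, and the number with unknown week-12 status is reported by arm.
- **Section 24:** the DSMB receives these deaths along with the rest of its data.

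This changes data collection and reporting only. It leaves the reasons for discontinuation, the referral pathways and the supplement regimen untouched. The cost is protocol wording, one phone call or home visit for each child who left early, and a few more SAE reports. House locations are already mapped and phone contacts already requested, so no new system is needed.
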